##### Home exercise component

Group exercise sessions will be supplemented by 30 minutes of home cardiovascular exercise, 3-4 days/week at a rating of perceived exertion (RPE) of 3-5 on the Borg 0-10 scale [81,82].

***Education component ***One 1.5-hour group session will be conducted weekly by a multi-disciplinary team of health professionals. The schedule for the educational sessions and topics of discussion are outlined in Table 2. Family members/caregivers of participants will be encouraged to attend. Powerpoint slides will be used to ensure consistency of information across sites. Participants will also have access to scheduled grocery shopping tours and cooking demonstrations to further support program objectives.

**Table 2 T2:** Schedule and discussion topics for educational sessions.

Week 1	Heart healthy eating: The basics
Week 2	Setting of health-related goals

Week 3	Exercise: The basics

Week 4	Cardiovascular risk factors and BP self-monitoring

Week 5	Nutrition: Building on the basics (including a 3-day food record analysis by the dietician)

Week 6	Exercise: Building on the basics

Week 7	Cardiovascular medications

Week 8	Healthy weight

Week 9	Smoking cessation

Week 10	Stress & coping

Week 11	Fine-tuning healthy eating

Week 12	Wrap-up

##### Intervention audits

All professionals involved in delivering PREVENT will receive standardized training to ensure consistency of program delivery across sites. To appraise the actual level of consistency, audits will be conducted at random intervals by the trial coordinator. Any deviations from the protocol will be rectified by the site PREVENT team.

##### Post-program follow-up

After the 12-week program, PREVENT participants will be provided with a written maintenance program based on their long-term goals. Participants will be requested to maintain their health passport and will be phoned monthly by the site coordinator until the 12-month follow-up as a means of monitoring of use of health passport, health status, health care utilization and adherence to the maintenance program.

### Data management and analysis

Data collected at each site will be recorded on standardized forms and entered into a secure database using a centralized, web-based data entry system that contains quality control checks (e.g., range checks, notification of missing data). An independent Data Safety and Monitoring Board, consisting a cardiologist, neurologist and a statistician, has been set up to review mid-point results (or at any time that a serious adverse event occurs) and inform the investigators on issues of trial safety.

Descriptive statistics will be calculated for dependent and independent variables. Demographic and clinical characteristics of subjects in the experimental and control groups will be compared on admission using 2-sample t-tests (continuous data) and Chi-square analysis (nominal data). Nonparametric methods will be used when assumptions of normality are violated. Similar analyses will be used to compare characteristics of (i) patients who consent to participate versus those who do not; (ii) subjects who complete the study versus those who withdraw, in order to determine the representativeness of the sample. A mixed effects analysis of variance with repeated measures will be used to model the treatment effects for variables that are interval or ratio and conform to the assumptions of normality (i.e., BP, waist girth, total cholesterol, HDL-C, LDL-C, triglycerides, serum glucose, hemoglobin A1c, peak VO_2_, Six-Minute Walk Test, step counts). Non-parametric tests (Mann Whitney and Kruskall Wallis tests) will be used for ordinal level data (i.e., International Physical Activity Questionnaire, Fatigue Assessment Scale, Montreal Cognitive Assessment, Hospital Anxiety and Depression Scale, Pittsburg Sleep Quality Index, Goal Attainment Scaling) or where a normal data distribution is not found. To control for baseline differences between groups, variables that are significantly different at baseline will serve as covariates in the analyses. Data will be analyzed on an intention-to-treat basis. Significant omnibus effects will be probed with t-tests, using the Bonferroni correction to control for multiple comparisons. Multiple regression will be conducted where appropriate to examine relationships among variables. Software will include Access and SAS version 9.1. Alpha level will be < 0.05.

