### Study Design

This is a two parallel group, four-site, single-blinded, randomized trial with group assignment stratified using the Stroke Prognosis Instrument II (SPI-II) [5]. Figure 1 illustrates the sequencing of the study protocol.

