### Outcome Measurement

Given the long duration and multi-modal nature of the interventions, a range of outcome measures will be used to ensure evaluation of relevant variables that span the domains of the International Classification of Functioning [66]. The variables and measurement tools that will be employed are summarized in Table 1. These measures were selected based on the primary and secondary aims of the trial, clinical relevance, psychometric qualities, and feasibility (availability, cost and administration time). Evaluations will be conducted over a 2-day assessment period at baseline, post-intervention, six months, and 12 months by trained assessors blinded to knowledge of study hypotheses and group assignment. At each assessment the assessors will be asked to record their 'guess' as to the group assignment of each participant.

**Table 1 T1:** Outcome variables, measurement tools and assessment schedule

Variable	Measurement tool	Baseline	Post-intervention	6-month follow-up	12-month follow-up
*Primary measures*					

Blood pressure	Sphygmomanometer [67]	√	√	√	√

Waist girth	Tape measure [68]	√	√	√	√

Lipid profile*	Biochemical analysis	√	√	√	√

Fasting serum glucose	Biochemical analysis	√	√	√	√

Haemoglobin A1c	Biochemical analysis	√	√	√	√

*Secondary measures*					

Aerobic fitness	Peak VO_2 _using maximal treadmill stress test (ramp protocol)	√	√		√

Lower extremity function	Short Physical Performance Test [69]	√	√	√	√

Walking endurance	Six-Minute Walk Test [70]	√	√	√	√

Physical activity	Step Watch™accelerometers	√	√		√

	International Physical Activity Questionnaire [71]	√	√	√	√

Fatigue levels	Fatigue Assessment Scale [72]	√	√	√	√

Cognition	Montreal Cognitive Assessment [73]	√			√

Mental health	Hospital Anxiety and Depression Scale [74]	√	√	√	√

Quality of sleep	Pittsburg Sleep Quality Index [75]	√	√	√	√

Tobacco use	Self-report, using a health passport	√	√	√	√

Health care utilization	Self-report, using a health passport	√	√	√	√

Medication adherence	Self-report, using a health passport	√	√	√	√

Health-related quality of life	Medical Outcomes Study Short-form 36-item Questionnaire [76]	√	√		√

Health-related goals	Goal Attainment Scaling [77]	√	√	√	√

Secondary vascular events**	Health record abstraction	√	√	√	√

*Includes total cholesterol, high-density lipoprotein cholesterol (HDL-C), low-density lipoprotein cholesterol (LDL-C), triglycerides

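### The rank tests named for the scale outcomes, and for any outcome found non-normal, cannot carry the promised covariate adjustment and leave the repeated visits unused

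*Protocol article*

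**What the plan says.** All analysis statements below come from the protocol article, section *Data management and analysis*.

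- **Interval or ratio outcomes.** "A mixed effects analysis of variance with repeated measures will be used to model the treatment effects for variables that are interval or ratio", provided that they also meet normality. All primary variables are listed here by name, including triglycerides, serum glucose and hemoglobin A1c.
- **Scale outcomes.** "Non-parametric tests (Mann Whitney and Kruskall Wallis tests) will be used for ordinal level data". The scales named are: "International Physical Activity Questionnaire, Fatigue Assessment Scale, Montreal Cognitive Assessment, Hospital Anxiety and Depression Scale, Pittsburg Sleep Quality Index, Goal Attainment Scaling". *Table 1* classes all six as secondary.
- **Fallback.** The same tests apply "or where a normal data distribution is not found". This clause is not limited to secondary outcomes.
- **Adjustment.** The next sentence says that "variables that are significantly different at baseline will serve as covariates in the analyses". It is not limited to the mixed model.

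On the design, *Study Design* says: "This is a two parallel group, four-site, single-blinded, randomized trial". *Outcome Measurement* says: "Evaluations will be conducted over a 2-day assessment period at baseline, post-intervention, six months, and 12 months". In *Table 1*, five of the six scales are ticked at all four times. The Montreal Cognitive Assessment (MoCA) is ticked at baseline and 12 months only.

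**The concern.** The named tests do not fit the rest of the paragraph or the data to be collected.

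1. Mann-Whitney and Kruskal-Wallis compare independent groups on one value per person and have no place for a covariate. The adjustment promised in the next sentence cannot be carried out inside them.
2. Five scales have three follow-up values per person and MoCA has one. A test at one visit ignores the other visits. It also ignores baseline unless change scores are ranked, and the text does not say whether they are.
3. The fallback makes the analysis of a primary variable depend on a look at its distribution. Triglycerides, glucose and hemoglobin A1c are the obvious candidates. A variable that is moved loses the repeated-measures model, and the comparison changes from a difference in means to a rank comparison.

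At stake are precision for the scales and, for the primary laboratory outcomes, a method that is settled before the data are seen.

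**Working it through.** **Consistency of the text.** Set side by side, the rank-test sentence covers six scales plus any non-normal outcome, and the covariate sentence covers the analyses without exception. No rank ANCOVA, ordinal regression, transformation or change-score analysis is named that would reconcile the two. With two groups, Kruskal-Wallis is the same test as Mann-Whitney.

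**Inputs.** From *Sample Size*: difference 4.9 mmHg, SD 13.4, 119 per group, two-sided 0.05, 80% power. The documents give no correlation between visits. I assume ρ = 0.3 to 0.7, equal between all visits. The blood-pressure effect, 4.9/13.4 = 0.366 SD, serves only as a yardstick, since no effect is stated for any scale.

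**The plan's own figure.** The exact t-test gives 80.2% power at 119 per group and 79.9% at 118, so 119 reproduces.

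**Formulas (normal approximation).** Power = Φ(0.3657 × √(119/2) / √v − 1.960), where v is the variance relative to a t-test on one visit.

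- t-test, v = 1: 0.3657 × 7.714 = 2.821; Φ(0.861) = 80.5%.
- Mann-Whitney at one visit, v = π/3 (efficiency 0.955): 2.756; Φ(0.796) = 78.7%.
- Mann-Whitney on change scores, v = (π/3) × 2(1 − ρ).
- One visit adjusted for baseline, v = 1 − ρ². At ρ = 0.5: 2.821/√0.75 = 3.257; Φ(1.297) = 90.3%.
- Mean of three follow-ups adjusted for baseline, v = (1 + 2ρ)/3 − ρ². This assumes the same effect at each visit.

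| Power, normal data | ρ = 0.3 | ρ = 0.5 | ρ = 0.7 |
|---|---|---|---|
| Mann-Whitney, one visit | 78.7% | 78.7% | 78.7% |
| Mann-Whitney, change score | 64.4% | 78.7% | 94.5% |
| Baseline-adjusted, one visit | 84.1% | 90.3% | 97.7% |
| Baseline-adjusted, mean of three visits | 98.9% | 99.2% | 99.9% |

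For 80% power at one visit, Mann-Whitney needs 124 per group. The baseline-adjusted model needs 107, 89 and 60. Ranking alone costs under 2 points (80.5% to 78.7%); the rest of the loss comes from not using baseline and the other visits.

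**Simulation on a scale.** For a near-symmetric 0–21 integer scale, one follow-up visit and ρ = 0.3 to 0.7, power was 77–79% for Mann-Whitney, 64–94% for Mann-Whitney on change scores, 83–97% for ANCOVA and 81–96% for rank ANCOVA. Type I error was about 5% for both Mann-Whitney and ANCOVA.

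**Simulation on strongly skewed (lognormal) data, one visit.**

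| Power | ρ = 0.3 | ρ = 0.5 | ρ = 0.7 |
|---|---|---|---|
| Mann-Whitney | 78.4% | 79.3% | 79.6% |
| ANCOVA, raw scale | 70.0% | 77.8% | 87.8% |
| Rank ANCOVA | 80.8% | 88.5% | 96.2% |

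These data are normal after taking logs, so ANCOVA on the log scale returns to the 84.1%, 90.3% and 97.7% of the first table.

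**The case against.** The strongest reply is that the planned test is valid and that the rest is a preference for efficiency. Much of this stands.

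- *Baseline cannot be used at all.* A reader might infer this, but change scores can be ranked. At ρ = 0.7 that recovers most of the loss; at ρ = 0.3 it does worse than ignoring baseline. The text does not say which is meant, and neither version takes covariates.
- *Repeated scores will be treated as independent.* Naming Kruskal-Wallis in a two-arm trial may suggest pooling across visits. Pooling three visits would give a type I error of about 17% at ρ = 0.6. The protocol nowhere proposes it, so it is no part of this point.
- *A linear model is always better.* The lognormal results show otherwise on the raw scale at ρ of 0.5 or lower. Rank ANCOVA keeps its advantage there.
- *Rank tests give no effect in scale units.* A Hodges-Lehmann shift supplies one.
- *The trial loses its stated power.* The sample size rests on a t-test for systolic blood pressure. No power is claimed for any scale, and the named scales are secondary.
- *The covariate sentence may mean only those analyses that accept covariates.* This is a fair reading, and the paragraph also allows multiple regression where appropriate. It would still leave the scale comparisons unadjusted, and the text does not say so.

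The reply does not answer the fallback clause. The primary variables are listed under the mixed model, but the same paragraph lets any of them leave it on the basis of their observed distribution. This is stated text, not a detail left to a fuller plan, so an analysis plan that followed it would inherit the switch.

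**Conclusion.** The point holds as a should-fix on analysis wording. The paragraph assigns tests that cannot do what its next sentence promises, and it leaves baseline and repeated visits unused or unspecified for the scales. It also makes the method for a primary laboratory outcome depend on a normality check.

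At one visit, with 119 per arm and 0.366 SD on a near-symmetric scale, the cost relative to baseline adjustment runs from about 5 power points at ρ = 0.3 (78.7% against 84.1%) to 19 at ρ = 0.7 (78.7% against 97.7%). If change scores were ranked, the gap would be about 20, 12 and 3 points at ρ = 0.3, 0.5 and 0.7. These figures rest on assumed correlations and a borrowed effect size. For MoCA, with a single follow-up, only the baseline and covariate part applies. The documents do not support an invalid test, an inflated error rate or a wrong sample size.

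**What to change.** 1. Keep every primary laboratory outcome in the repeated-measures mixed model with its baseline value as a covariate. State in advance which skewed variables are analysed on the log scale. Delete the clause that switches method when normality is not found.
2. Analyse the scale outcomes with a baseline-adjusted longitudinal model: proportional-odds or another ordinal model, a rank-based model, or a linear model for summed scores. Use a single-follow-up version for MoCA. Include the SPI-II randomisation stratum as a covariate.
3. Keep Mann-Whitney as a sensitivity analysis, stating whether follow-up or change scores are ranked. Drop Kruskal-Wallis.

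The cost is a change of wording and slightly more analysis work, plus a proportional-odds or linear-scale assumption, which the Mann-Whitney sensitivity analysis helps to check. No new data or patients are needed. The article gives the trial's status as still enrolling and already names SAS as the software.

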**Methods/Design:**

A single blind, randomized controlled trial will be conducted at two sites to compare the effectiveness of a program of rehabilitative exercise and education versus usual care in modifying vascular risk factors in adults after NDS/TIA. 250 adults within 90 days of being diagnosed with NDS/TIA will be randomly allocated to a 12-week program of exercise and education (PREVENT) or to an outpatient clinic assessment and discussion of secondary prevention recommendations with return clinic visits as indicated (USUAL CARE). Primary outcome measures will include blood pressure, waist circumference, 12-hour fasting lipid profile, and 12-hour fasting glucose/hemoglobin A1c. Secondary measures will include exercise capacity, walking endurance, physical activity, cognitive function, depression, goal attainment and health-related quality of life. Outcome assessment will be conducted at baseline, post-intervention, and 6- and 12-month follow-ups. Direct health care costs incurred over one year by PREVENT versus USUAL CARE participants will also be compared. Ethical approval for the trial has been obtained from the relevant Human Research Ethics Boards.

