A major thrust in public health over the next decade will be to focus attention on identification and management of vascular risk factors. Although primary prevention is the ultimate goal, resources will need to be allocated to those who are at high risk and most likely to gain the greatest benefit. One such group is people who have experienced a NDS/TIA. The main objective of the PREVENT trial is to determine whether the timely delivery of a comprehensive program of secondary stroke prevention services and coordinated care can improve long-term vascular risk reduction for patients after NDS or TIA. The primary aim is to compare the effectiveness of a program of rehabilitative exercise and education (PREVENT) versus usual care (USUAL CARE) in reducing vascular risk factors in people who have had a NDS or TIA. Secondary aims are to compare between PREVENT and USUAL CARE groups (i) exercise capacity, walking endurance, daily physical activity, number of cigarettes smoked daily, medication adherence; (ii) fatigue, cognitive function, depression, health-related goal attainment and health-related quality of life; (iii) direct health costs incurred over a 1-year period; (iv) reduction in secondary vascular events, within the limitations in sample size and trial duration. We anticipate that, in comparison to USUAL CARE, timely delivery of PREVENT will produce clinically important and sustainable improvements in the outcome variables.

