## Discussion

The main focus of PREVENT Trial is to investigate the role of aerobic exercise, education and lifestyle counselling in reducing vascular risk factors of people after TIA or NDS. This trial will contribute much needed evidence to begin answering important clinical questions regarding the role of non-pharmacological interventions, modelled after cardiac rehabilitation programs, in preventing second stroke in the often under-served patient populations involved in this trial. Although the trial is not sufficiently powered to determine the effectiveness of PREVENT on hard clinical outcomes such as second vascular events or death, we will compare occurrence rates between groups in order to inform future, larger scale trials.

This multi-site RCT will also explore the impact of the PREVENT program on cardiovascular fitness, walking tolerance, fatigue, cognition, mental health, quality of sleep, medication adherence, tobacco use, and health-related quality of life, which may be mitigating factors in reducing vascular risk factors, and, ultimately, stroke recurrence. As well, comparison of the direct health costs of the PREVENT and USUAL CARE groups over the course of the study will provide important preliminary information related to cost effectiveness and sustainability of multi-modal, behavioral interventions such as PREVENT.

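### The general rule for non-normal data does not exempt costs, so unless another plan overrides it, the one-year cost comparison falls to a rank test that does not compare mean costs

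*Protocol article*

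**What the plan says.** The cost comparison appears in three places in the protocol article:

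- Abstract, Methods/Design: "Direct health care costs incurred over one year by PREVENT versus USUAL CARE participants will also be compared".
- Background, secondary aim (iii): the arms are to be compared on "direct health costs incurred over a 1-year period".
- Discussion: the comparison "will provide important preliminary information related to cost effectiveness and sustainability" of interventions of this kind.

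Data management and analysis gives two routes for comparing outcomes between arms:

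- A mixed-effects analysis of variance with repeated measures, to "model the treatment effects for variables that are interval or ratio and conform to the assumptions of normality". A list of variables follows.
- A second route: "Non-parametric tests (Mann Whitney and Kruskall Wallis tests) will be used for ordinal level data", again with a list, and then the extension "or where a normal data distribution is not found".

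Costs are in neither list, and no exception is written for them. The section names no method specific to costs. Its only other candidate is multiple regression to explore relationships among variables, which is not a plan for comparing arms. In Table 1 (Outcome Measurement) the nearest entry is resource use: "Health care utilization Self-report, using a health passport".

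**The concern.** The extension to the second route is worded for any variable that turns out non-normal. Costs per person cannot be negative and usually include a few very large values from admissions, so they would very likely meet that condition. The rule then selects a test that answers a different question from the stated aim.

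Mann-Whitney asks whether a randomly chosen PREVENT participant tends to cost more than a randomly chosen USUAL CARE participant. A payer judging cost-effectiveness or sustainability needs the difference in arithmetic mean cost, because the mean times the number treated gives the total bill.

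This design can pull the two questions apart. Under Interventions, PREVENT participants are offered 2 × 12 = 24 group exercise sessions, 12 education sessions and monthly calls until month 12. That is a moderate cost for nearly everyone. Any saving would come mainly from a few people who avoid an expensive event. The moderate cost shifts most ranks, while the few large savings hardly shift ranks but can dominate the mean. At stake is a cost result that could point against PREVENT when its mean cost is equal or lower.

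**Working it through.** **The plan's own figures.** The documents give no cost figure to reproduce. The only plan inputs used are 125 participants per arm and a two-sided 0.05 level (Sample Size). The underlying 119 per arm for systolic blood pressure does reproduce: the exact t-test power at 119 is 0.802. It is not affected by this point.

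**Which rule reaches costs.** Cost is a ratio-scale variable. If it conforms to normality, the first route applies. If it does not, the extension to the second route applies. No third route is stated for a between-arm comparison of costs.

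**Set 1: near-equal true means.** All cost inputs are assumptions.

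- Cost = lognormal background cost + 15,000 if hospitalised + programme cost (PREVENT only).
- True mean difference (PREVENT minus USUAL CARE) = programme cost − 15,000 × (hospitalised share in USUAL CARE − share in PREVENT).
- Scenario A: programme 1,000; hospitalised 15% versus 8%. Difference = 1,000 − 15,000 × 0.07 = −50.
- Scenario B: programme 500; hospitalised 10% versus 6.7%. Difference = 500 − 15,000 × 0.033 = +5.

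Share of simulated trials in which Mann-Whitney declares PREVENT significantly dearer:

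| Assumed background cost | Scenario A | Scenario B |
|---|---|---|
| Mean 1,500, CV 1 | over 99% | about 93% to 95% |
| Mean 5,000, CV 1 | about 32% | about 14% |
| Mean 8,000, CV 1.5 | about 14% | about 8% |

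With equal means, about 2.5% would be expected in that direction. In the first row, a Welch comparison of means rejected in about 5% of trials over both directions, as it should.

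**Set 2: PREVENT truly cheaper.** Assumed: lognormal routine cost with median 1,500 and log-SD 0.8, 20% of USUAL CARE hospitalised, and a variable hospitalisation cost with the mean shown.

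- Programme 1,000; PREVENT hospitalised 10%; mean hospital cost 15,000. Difference = 1,000 − 15,000 × 0.10 = −500. Mann-Whitney declared PREVENT dearer in 91% of trials; the comparison of means did so in 0.5%.
- Programme 500; PREVENT hospitalised 10%; mean hospital cost 20,000. Difference = 500 − 20,000 × 0.10 = −1,500. Mann-Whitney declared PREVENT dearer in 23%; the comparison of means in 0.1%.

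Over five such scenarios the wrong-direction rate ran from 23% to 91%. The chance that a random PREVENT participant cost more than a random USUAL CARE participant was 0.55 to 0.62, although PREVENT's mean was lower.

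**If programme cost is left out.** The wrong-way result no longer arises by this mechanism, but the rank test is then insensitive to a real saving. With a true saving of 15,000 × 0.07 = 1,050, it detected the saving in 17% of trials, against 38% for a comparison of means.

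**The case against.** The strongest reply is that the analysis section never mentions costs. Both routes carry explicit lists of variables, and several other outcomes in Table 1, such as the SF-36, tobacco use and vascular events, are in neither list, so the section plainly does not cover every comparison in the trial. No unit costs, perspective or costing method appear anywhere. The natural inference is that the economic analysis is described elsewhere, and a journal article may leave it there.

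Much of this stands. Costs reach the rank test only through the general wording, and an unseen economic or analysis plan could override it. What does not fall away is that the one published rule able to reach non-normal costs selects a test that does not serve the stated aim. That is a matter of what the rule says, and not only of what is left out.

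Three stronger inferences are tempting and are not supported:

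- That the protocol has assigned costs to Mann-Whitney. It has not named them.
- That no mean costs would be reported. The section promises descriptive statistics, so arm means may well appear. What is not stated is a confidence interval for their difference.
- That the wrong answer is nearly certain. Rates above 90% depend on a low background cost relative to programme cost, and the documents give no reason to prefer 1,500 over 5,000 or 8,000.

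**Conclusion.** The point holds in a conditional form. Read as written, and unless a plan not shown overrides it, the rule sends skewed costs to a rank test that does not assess the difference in mean cost and can point the wrong way.

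The size cannot be fixed from the documents. With near-equal true means and 125 per arm, the rate of declaring PREVENT dearer ran from about 8% to over 99%, against about 2.5% expected. Every scenario in that table exceeded the expected rate, but how far depends on the assumed background and programme costs.

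The conclusion rests on three assumptions: that costs are right-skewed, that programme cost is counted in the PREVENT total, and that savings come from a few avoided admissions. It concerns a secondary aim that the article itself treats as preliminary. It is worth correcting because the correction is cheap; it does not threaten the trial's main conclusions.

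**What to change.** Add one or two sentences to the analysis section, or confirm that an existing plan already contains them:

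- Costs are exempt from the normality and rank-test rule.
- The arms are compared on arithmetic mean one-year direct cost per randomised participant.
- The mean difference is reported with a 95% confidence interval, for example by bootstrap or a generalised linear model. Medians are descriptive only.
- State whether the cost of delivering PREVENT (sessions and monthly calls) is included in the PREVENT total.

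This needs no extra participants or visits. If programme delivery is to be included, its cost must be obtained; the article does not say from where. The article gives the trial's status as still enrolling, so the wording could be settled before cost data are analysed.

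The downside is a wide interval. In the two Set 2 scenarios shown, a comparison of means correctly declared PREVENT cheaper in only about 6% and 27% of trials. That width reflects the real uncertainty about mean cost at this sample size.

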#### Sample Size

Systolic blood pressure, the most robust predictor of secondary vascular events [14], was selected as the outcome variable for sample size calculation. Using estimates obtained from our pilot study, a sample size of 119 in each group will have 80% power to detect a difference in means of 4.9 mmHg, assuming that the common standard deviation is 13.4 using a two group t-test with a 0.05 two-sided significance level. We have allowed for an overall attrition rate of 5% [55], thus increasing the sample size to 125 per group (250 in total). The trial will not be sufficiently powered to determine the effectiveness of the PREVENT intervention in reducing recurrent TIA, stroke or cardiac events. Thus, it will be exploratory in this regard and will help inform the design of a future, more extensive trial.

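### Covariates are to be picked by baseline significance tests, which makes the model data-dependent and gives up precision that the baseline values could supply

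*Protocol article*

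**What the plan says.** All of the relevant text is in the protocol article, mostly under Data management and analysis. The arms are first tested against each other at entry: "Demographic and clinical characteristics of subjects in the experimental and control groups will be compared on admission using 2-sample t-tests", with chi-square tests for nominal variables. The results then decide the adjustment: "To control for baseline differences between groups, variables that are significantly different at baseline will serve as covariates in the analyses". The main model for the interval-scale outcomes is described so: "A mixed effects analysis of variance with repeated measures will be used to model the treatment effects". The article does not say whether the baseline measurement is a level of time in that model. For other outcomes, "Non-parametric tests (Mann Whitney and Kruskall Wallis tests) will be used for ordinal level data". The only significance threshold given is "Alpha level will be < 0.05".

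No section names a covariate in advance. Neither the outcome's baseline value nor the SPI-II stratum used under Randomization Procedures is mentioned. Under Sample Size, systolic blood pressure (SBP) "was selected as the outcome variable for sample size calculation", and the calculation is a plain comparison of two means.

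**The concern.** After concealed random allocation, any baseline difference between arms is chance. A p-value for that difference says nothing about whether the variable predicts the outcome, and prediction is what makes a covariate worth having. The rule therefore fails in two ways:

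- It admits variables flagged by chance, prognostic or not.
- It nearly always passes over the baseline value of the outcome itself, usually the most useful covariate available.

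The final model is also known only after the data have been examined. If baseline is one of the repeated responses, a flagged outcome would appear both as response and as covariate.

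At stake are the precision of every mixed-model comparison, including those for the primary risk factors, and how far a chance gap at entry distorts the estimate in the one trial that will be run.

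**Working it through.** **Inputs from the article.** Sample Size: difference 4.9 mmHg, SD 13.4, 119 per group, 80% power, two-sided 0.05, 5% attrition, 125 per group enrolled. Threshold for the baseline tests: 0.05, the only alpha stated.

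**Assumptions.** Correlation r between baseline and follow-up SBP is 0.3, 0.5 or 0.7. The figure 13.4 is the SD of follow-up SBP, and baseline SBP has the same SD. One follow-up visit is considered.

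**1. The plan's own figure.** SE = 13.4 × √(2/119) = 1.737, and 4.9/1.737 = 2.82. The exact two-sample t calculation gives 80.2% power at 119 per group and 79.9% at 118, so 119 is reproduced. Attrition: 119/0.95 = 125.3, in line with 125.

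**2. How often baseline SBP becomes a covariate.** By construction about 5% of trials (4.8 to 5.1% in simulation, 20,000 trials per setting). If 20 to 30 baseline variables were tested (an assumed count), 20 × 0.05 = 1 to 30 × 0.05 = 1.5 would be flagged by chance.

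**3. Size of a chance gap in baseline SBP.** With 125 per group, SE = 13.4 × √(2/125) = 1.695. The median absolute gap is 0.674 × 1.695 = 1.1 mmHg. The largest non-significant gap is 1.96 × 1.695 = 3.3 mmHg.

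**4. What a non-significant gap does to the comparison.**
- If baseline is not a response level, r × gap passes into the follow-up difference. At most this is 1.0/1.7/2.3 mmHg for r = 0.3/0.5/0.7, or 20/34/47% of 4.9. At the median gap it is 0.3/0.6/0.8 mmHg.
- If baseline is a time level and the effect is group-by-time, the gap is subtracted in full and so over-corrected by (1 − r) × gap. At most this is 2.3/1.7/1.0 mmHg.

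**5. Power at 119 per group.** With constant adjustment the residual SD is 13.4 × √(1 − r²) = 12.8/11.6/9.6. By normal approximation, power is 84.1/90.3/97.7%. The simulation, in which a flagged baseline is adjusted for by ANCOVA, gave:

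| Analysis | r = 0.3 | r = 0.5 | r = 0.7 |
|---|---|---|---|
| Baseline always a covariate | 83.9% | 89.8% | 97.6% |
| Rule, baseline not a response | 80.8% | 81.2% | 81.9% |
| Rule, baseline a time level (change contrast) | 67.7% | 81.2% | 95.6% |

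The loss is about 3, 9 and 16 points on the first reading, and about 16, 9 and 2 on the second.

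**6. Type I error.** Overall under the rule it is 4.8/4.2/3.7% (baseline not a response) or 4.0/4.5/4.7% (change contrast). Among trials with a sizeable but non-significant gap (|t| from 1.28 to 1.97) it is 6.2/8.7/12.2% or 10.1/8.9/7.1%, against 4.8/5.7/4.3% with constant adjustment.

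**7. If 13.4 is instead the SD of change.** The adjusted SD is 13.4 × √((1 + r)/2) = 10.8/11.6/12.4. Power with constant adjustment is 93.8/90.3/86.4%, against the designed 80% for an unadjusted comparison of changes.

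**The case against.** The strongest reply is that the repeated-measures model may already use baseline. Table 1 schedules a baseline measurement for every primary outcome, so time could well have baseline as its first level, with treatment judged by group-by-time. A reader might infer from the covariate rule that baseline SBP is ignored and that imbalance goes uncorrected. The article does not support that, because it leaves the point open. On this reading the gap is over-corrected rather than untouched, and at r = 0.7 only about 2 points of power are lost. That stands, and it is why both readings are shown. It does not rescue the rule, since fixed adjustment has more power at every assumed r on either reading.

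Second, the article does not say that flagged variables are the only covariates, and a separate analysis plan may list more. That also stands as far as it goes. If that plan always includes the baseline value, most of the power loss disappears. But what is criticised here is a stated rule, not a missing list, and the rule would still add covariates picked by chance.

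Third, 3.3 mmHg is the edge of non-significance, not a typical gap; the median is about 1.1 mmHg. This is correct.

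Fourth, an unadjusted follow-up comparison still has the 80% power planned under Sample Size, and randomisation keeps it unbiased on average. Both statements are true. They limit the seriousness of the defect without defending the rule.

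**Conclusion.** The point holds as a defect in a stated analysis rule. Its cost is lost precision, bias conditional on the imbalance actually seen, and a model that is not fixed in advance. On the follow-up SD reading, the power forgone runs from about 2 to 16 points, depending on r and on whether baseline is a time level. At r = 0.5 it is about 9 points either way.

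Two stronger conclusions are not supported. A reader might infer a raised false-positive rate, but the overall type I error is at or below 5%; it rises only within the subset of trials with a sizeable unflagged gap. A reader might also infer that the trial misses its planned power. That follows only for a change contrast with r below 0.5 and 13.4 read as the follow-up SD.

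The sizes rest on an r that the article does not give, on the reading of 13.4, and on a single follow-up visit for SBP. The same logic applies to waist, lipids, glucose and haemoglobin A1c, but its size there was not calculated.

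**What to change.** Delete the significance-based rule. For every outcome analysed with the mixed model, state in advance that the baseline value of that outcome and the SPI-II randomisation stratum are covariates and that the response consists of the post-baseline visits only. An equivalent choice is a mixed model with the baseline means constrained to be equal across arms. Either applies whatever imbalance is observed. The baseline table may stay as description, but its tests should not select covariates.

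The Mann-Whitney and Kruskal-Wallis tests take no covariate in standard form. For those outcomes, either name a baseline-adjusted alternative such as rank ANCOVA or say that they are left unadjusted.

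The cost is a few sentences in the analysis section plus that decision on the rank-test outcomes. No extra patients or measurements are needed for the mixed-model outcomes. The article describes the trial as still enrolling, so the change can be made before the analysis.
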